## Abstract

**Introduction:**

In a small percentage of patients, pulmonary nodules found on CT scans are early lung cancers. Lung cancer detected at an early stage has a much better prognosis. The British Thoracic Society guideline on managing pulmonary nodules recommends using multivariable malignancy risk prediction models to assist in management. While these guidelines seem to be effective in clinical practice, recent data suggest that artificial intelligence (AI)-based malignant-nodule prediction solutions might outperform existing models.

**Methods and analysis:**

This study is a prospective, observational multicentre study to assess the clinical utility of an AI-assisted CT-based lung cancer prediction tool (LCP) for managing incidental solid and part solid pulmonary nodule patients vs standard care. Two thousand patients will be recruited from 12 different UK hospitals. The primary outcome is the difference between standard care and LCP-guided care in terms of the rate of benign nodules and patients with cancer discharged straight after the assessment of the baseline CT scan. Secondary outcomes investigate adherence to clinical guidelines, other measures of changes to clinical management, patient outcomes and cost-effectiveness.

**Ethics and dissemination:**

This study has been reviewed and given a favourable opinion by the South Central—Oxford C Research Ethics Committee in UK (REC reference number: 22/SC/0142).

Study results will be available publicly following peer-reviewed publication in open-access journals. A patient and public involvement group workshop is planned before the study results are available to discuss best methods to disseminate the results. Study results will also be fed back to participating organisations to inform training and procurement activities.

**Trial registration number:**

NCT05389774.

STRENGTHS AND LIMITATIONS OF THIS STUDYThis is a prospective study examining the use of artificial intelligence (AI)-based computer-aided diagnosis (CADx) for pulmonary nodules.This study will examine the clinical utility of an AI-based CADx tool for pulmonary nodule management.The study is non-interventional in nature.The analysis of some of the secondary objectives is exploratory due to potential sample size restrictions.

## Introduction

From 2017 to 2019, lung cancer caused 34 771 deaths in the UK per annum, more than prostate and bowel cancer combined (28 846), the next most common causes of cancer death. Over the same period, there were 24% more deaths in women from lung cancer than from breast malignancy (14 140 vs 11 415).^1^ This is because almost three-quarters of people with lung cancer present with stage III or IV disease when the prognosis is poor despite recent advances in systemic anticancer treatment. Lung cancer detected at an early stage, usually by thoracic CT, has a much better prognosis. Screening with low-dose CT thorax has recently been confirmed to reduce lung cancer and all-cause mortality.^2–4^ Central to the success of screening is the accurate management of pulmonary nodules, which may represent early-stage lung cancer, but are far more often benign. Pulmonary nodules are also a common finding on CT scans done for other reasons. In some settings, this may yield more early lung cancers than screening. Identifying malignant pulmonary nodules on CT scans is the primary way to detect lung cancer at stage I, when the prognosis is best. By definition, isolated pulmonary nodules without other lung changes are stage I if proven to be lung cancer. Currently, most nodules are detected outside screening programmes in the UK, providing an important rationale for this study to address the effective management of these incidentally detected nodules.

The British Thoracic Society (BTS) guideline on managing pulmonary nodules was published in 2015.^5^ This guidance was the first to recommend semiautomated volumetry as the standard for nodule measurement and the use of multivariable malignancy risk prediction models to assist in management. While these guidelines seem to be effective in clinical practice,^6^ recent data suggest that artificial intelligence (AI)-based malignant-nodule prediction solutions appear to outperform existing multivariable models.^7 8^ This could result in a considerable reduction in the number of follow-up CT, which is much needed in the National Health Service (NHS), where current and forecasted demand for radiology services exceeds capacity.^9 10^

Optellum has developed and extensively validated an AI-based computer-aided diagnostic (CADx) tool for lung cancer prediction (LCP) in pulmonary nodules, which has UK Conformity Assessed marking under UK medical device regulations. The AI model underpinning the LCP is a convolutional neural network (CNN), referred to hereafter as the ‘LCP-CNN’. LCP-CNN was derived and internally validated using data from diverse populations from the USA and UK. The model was then externally validated in two independent cohorts of patients with incidentally detected pulmonary nodules, amounting to over 1500 patients in aggregate.^7 8^ The LCP-CNN demonstrated greater accuracy in these studies than the Brock and Mayo malignancy risk models (used in managing incidentally detected nodules in the UK and USA, respectively). The product is provided within the ‘Virtual Nodule Clinic’ (VNC), a software device used in the tracking, assessment and characterisation of incidentally detected pulmonary nodules.

The study aims to assess this new AI tool in a prospective real-world setting in the UK. This will be done by calculating malignancy risk using LCP and measuring how management would differ if it was governed by the risk provided. The aim is to provide evidence as to whether LCP should be the new standard of care in pulmonary nodule management.

## Methods and analysis

The study acronym is ‘DOLCE’ (Determining the impact of Optellum’s LCP artificial intelligence solution on service utilisation, health Economics and patient outcomes).

### Design and setting

DOLCE is a multicentre prospective observational cohort study recruiting patients with 5–30 mm solid and part-solid pulmonary nodules incidentally detected on thoracic CT scans performed as part of routine practice. The study aims to recruit 2000 patients from 12 centres.

Patients will be asked to consent to and be enrolled at twelve acute NHS hospital trusts in England. A recruitment period of 1 year is planned, with 1 year of follow-up to collect data and ascertain the ground-truth diagnosis of recruited patients.

The start date was March 2023 with the planned recruitment end date being February 2024. With 1 year of follow-up, this will mean a planned end date of February 2025.

### Clinical pathway

This is a non-interventional study. There will be no anticipated change to the standard of care the recruited patients receive throughout the study’s duration. The potential impact of AI-modified management will be assessed by comparing routine clinical management with that which would have been conditional on the LCP risk score. The scores will be provided to clinicians after routine management decisions have been made, either during the same multi-disciplinary team (MDT) meeting or at a separate research meeting. A hypothetical clinical decision based on the LCP score will then be recorded.

### Study population

Patients who have undergone CT that has detected a pulmonary nodule and was performed for a reason other than suspicion of lung cancer will be reviewed for study eligibility (box 1).

Box 1Patient eligibility criteriaInclusion criteriaPatients aged 35 years or over.Patients with a baseline CT study with at least one incidentally detected solid or part-solid pulmonary nodule that is 5–30 mm in maximum axial diameter for the whole lesion, measured using manual electronic callipers, and that is not fully calcified. The solid component of the part-solid nodule must be ≥80% of the total nodule size.Patients with a baseline CT study which includes at least one series with acquisition parameters which meet Virtual Nodule Clinic requirements.The patient has a baseline CT study that includes at least one series that comprises at least one full-inspiration breath-hold scan without a high degree of contrast media and does not exhibit quality issues (eg, motion artefacts).Exclusion criteriaPatients who received a diagnosis of cancer in the last 5 years.Patients who have thoracic implants that adversely impact the imaging appearances of the nodule.Patients who have more than five reported pulmonary nodules of any size or type, excluding fully calcified nodules (a marker of prior granulomatous infection) or metastatic lung cancer.Patients who have one or more additional nodules that are already undergoing follow-up according to pulmonary nodule management standard care.Patients who have one or more additional nodules that are pure ground glass opacity of 5 mm in maximum axial diameter for the whole lesion measured using manual electronic callipers.Patients who have one or more additional nodules >30 mm in maximum axial diameter for the whole lesion measured using manual electronic callipers.Patients with part-solid nodules where the solid component is <80% of the total nodule size.

### AI model

The output of the LCP is a risk score that is an integer from 1 to 10 and forms part of Optellum’s VNC patient management software. A score of 1 indicates the nodule is highly likely to be benign, while a score of 10 is most likely to be malignant. The AI model underpinning the LCP is the LCP-CNN, the raw score available to researchers as a continuous value from 0 to 100, as previously reported. LCP-CNN was derived and internally validated using data from diverse populations from the USA and UK. The model was then externally validated in two independent cohorts of patients with incidentally detected pulmonary nodules, amounting to over 1500 patients in aggregate.^7 8^

In this study, the LCP will be compared with standard care in three ways:

LCP as an integer (1–10) risk score to aid physician decision-making (physician guided by AI score).LCP-CNN alone as a threshold-based rule-out recommendation (AI binary decision to discharge or not).LCP-CNN combined with a threshold-based rule-out recommendation to aid physician decision-making (physician guided by AI with binary recommendation to discharge or not).

### Data collection

Study teams at the 12 NHS Trusts from which patients will be recruited will identify eligible patients and obtain informed consent. Consent will be obtained verbally (for patients who would not normally come on-site as part of standard care) or via written consent. Consent will be sought to analyse standard-care CT scans, associated clinical meta-data collection and the health economics assessment.

Once a patient has given consent and enrolled into the study, their baseline CT scan will be sent to VNC. Authorised research staff will then log into VNC, select the nodules of interest and record the LCP score for that nodule. The local standard nodule service decision-makers will provide a standard-care decision for eligible, consented patients via their usual nodule management pathway. The standard-care decision for eligible consented patients will then be recorded in an electronic case report form (eCRF) without knowing the LCP score.

To assess LCP under scenario #1 as described under AI model, the clinical team will thereafter be given the LCP score and relevant patient data in the nodule MDT or as part of a separate research meeting. At this point, the clinical team should remain blinded to the outcome of any actual-care investigation (eg, positron emission tomography (PET)/CT scan, biopsy). Their decision on the next management step, had they been guided by the LCP score, will then be recorded in the eCRF. The clinical team will have the option to modify management at this point. Any modification of management will be recorded in the eCRF.

Subsequent follow-up images for each patient will be sent to the VNC over the course of their nodule follow-up, and the final nodule diagnosis will be recorded. Since standard patient care can sometimes deviate from BTS guidelines, all participating sites will also collect information on patient and nodule characteristics necessary to follow the BTS guidelines. In this way, AI-guided management can be compared with BTS-compliant management. Other data points necessary to evaluate service utilisation (eg, additional scans, biopsies and treatments for lung nodules or lung cancers) will also be recorded in the eCRF.

In line with Standard Protocol Items: Recommendations for Interventional Trials - Artificial Intelligence (SPIRIT-AI) guidelines, performance errors that would have happened if the LCP or LCP-guided decision-making were part of standard care will be analysed and reported as outcome measures for the primary objective of this study.

Evaluation of LCP as threshold-based tests (scenarios #2 and #3 as described under AI model), which require access to LCP-CNN values, will be performed as a batch at the end of the study follow-up period. The threshold will be defined prospectively based on values from training datasets of similar patient populations. The use of the recommendation with physicians making the decision will be evaluated via a separate research meeting at the end of the 12-month follow-up period.

For cost-effectiveness modelling, quality of life data will be collected by inviting patients to complete an EQ-5D-5L quality of life questionnaire at two time points: (a) as close as possible to the baseline CT scan on which their pulmonary nodule was detected and (b) at a 1-year time point afterwards. A participant diary about primary care usage will also be collected at the 1-year mark.

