### Ground truth diagnosis

Patients will be classified into whether they have benign or malignant nodules as follows:

Benign-nodule patients:By resolution or stability of all qualifying incidental pulmonary nodules as determined from volumetry-based measurement on imaging follow-up over 12 months.By histopathology from biopsy or surgery of all qualifying incidental pulmonary nodules (within 12 months of baseline CT scan).Malignant-nodule patients:By histopathology from biopsy or surgery (within 12 months of baseline CT scan) of at least one qualifying incidental pulmonary nodule.Probable benign-nodule patients:By resolution, stability or shrinkage of qualifying incidental pulmonary nodules that are not in ground-truth outcomes #1 or #2 above as determined from volumetry-based measurement on imaging follow-up conducted between 3 and 12 months after the baseline CT scan.By resolution, stability or shrinkage of qualifying incidental pulmonary nodules that are not in ground-truth outcomes 1 or 2 above as determined from diameter-based measurement on imaging follow-up conducted 12 months after the baseline CT scan (supplemented with a volume-based measurement of the nodule that will be performed for research purposes).Probable malignant-nodule patients:By clinical diagnosis of lung cancer, in whom a biopsy or resection is not possible, based on high clinical probability and who are registered at a lung cancer MDT/and/or receive non-surgical treatment (stereotactic ablative radiotherapy (SABR)/radiotherapy/microwave ablation).

Volumetry-based measurement of nodule stability—and hence a benign diagnosis—will be satisfied if the lung nodule volume on the follow-up CT scan was <125% of the lung nodule volume on the baseline CT scan.

If the standard care at a particular site does not incorporate volumetry-based measurements, the volumetric measurement will be applied as part of the research study to the relevant follow-up CT scans.

Any lung nodule patients who do not fall into either of the two ground-truth outcomes 1 or 2 above will be considered to have an indeterminate diagnosis at the time of analysis and will be analysed with and without the inclusion of the ground-truth outcomes in 3 and 4.

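### The baseline LCP score reaches the clinical team before the reference diagnosis exists, and no stated blind separates it from later work-up, research volumetry or diagnosis assignment

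*Protocol article*

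**What the plan says.** All references are to the protocol article.

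- **Data collection, order of decisions.** The standard-care decision "will then be recorded in an electronic case report form (eCRF) without knowing the LCP score". Then, at the nodule MDT or a separate research meeting, "the clinical team will thereafter be given the LCP score and relevant patient data". At that point "the clinical team should remain blinded to the outcome of any actual-care investigation". Next, "The clinical team will have the option to modify management at this point", and any change is entered in the eCRF.
- **Data collection, follow-up.** "Subsequent follow-up images for each patient will be sent to the VNC over the course of their nodule follow-up, and the final nodule diagnosis" is then recorded. The text does not say who assigns the diagnosis or what that person has seen.
- **Clinical pathway.** "There will be no anticipated change to the standard of care the recruited patients receive throughout the study’s duration".
- **Ground truth diagnosis.** Definite malignant needs histopathology within 12 months. Definite benign needs histopathology, or resolution or stability on volumetry over 12 months, where stable means a volume below 125% of baseline. Probable malignant is reached "By clinical diagnosis of lung cancer, in whom a biopsy or resection is not possible, based on high clinical probability", together with lung cancer MDT registration and/or non-surgical treatment. Where a site does not use volumetry, the study supplies it. Results are given both with and without the two probable categories.
- **AI model; Data collection.** The 1–10 LCP score is part of the VNC software and rests on the LCP-CNN. The threshold-based options are evaluated in one batch after follow-up ends.

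**The concern.** Both primary outcomes count discharges among patients whose cancer or benign status is fixed later. A comparison of LCP with standard care is fair only if that status is settled independently of both. Independence from LCP is not secured here, because the score is released to clinicians at the start of the period over which the diagnosis accrues, and they may act on it.

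For the cancer outcome, the likely direction favours LCP. A low score may lead to less tissue sampling, so that a cancer LCP would have discharged is never confirmed. A high score may lead to more sampling, so that cancers LCP flagged are found and credited to it.

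For the benign outcome the direction is mixed. A borderline volume read as stable in a low-score patient adds a correct LCP discharge. A low-score patient who has no further imaging as a result drops out of the definite benign group, which removes one.

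The same reference standard serves all three LCP options, and all three rest on the same model. Early release for the first option therefore touches the other two, although their own outputs are held back until follow-up ends.

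**Working it through.** **Step 1. Which directions are blinded?**

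| From | To | Stated blind |
|---|---|---|
| LCP score | Standard-care decision | Yes |
| Investigation results | LCP-guided decision | Yes |
| LCP-CNN threshold recommendation | Care during follow-up | In effect, by batch evaluation afterwards |
| 1–10 LCP score | Later work-up | None; management may be modified |
| 1–10 LCP score | Research volumetry | None |
| 1–10 LCP score | Assignment of diagnostic category | None |

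**Step 2. How could the score enter the reference standard?**

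| Route | What limits it | What remains |
|---|---|---|
| Who is biopsied or imaged to 12 months | Modifications after disclosure are recorded | Entry to a definite category depends on work-up chosen by a team that has the score |
| Volume near the 125% cut | The cut is fixed | The volume is measured; research staff record the score and the study supplies volumetry at some sites, with no separation of these tasks stated |
| Probable malignant | Results also given without this category | The analysis that includes it rests on clinical judgement that may draw on the score |

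**Step 3. How sensitive is the cancer outcome to a few diagnoses?** The Sample size section gives discordant cells of 0.4% (LCP discharges, Brock does not) and 2.6% (the reverse).

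First, the plan's own figure, by the McNemar formula with d = 0.026 − 0.004 = 0.022 and s = 0.026 + 0.004 = 0.030:

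n = [1.960·√s + 1.282·√(s − d²)]² / d² = (0.3395 + 0.2202)² / 0.000484 ≈ 647.

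The plan states 659, a 1.8% difference, so the cells are being read as intended.

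The article gives no cancer share. **Assume** 5% to 15% of 2000, that is 100 to 300 cancers:

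- LCP-only missed cancers: 0.004 × 100 = 0.4, to 0.004 × 300 = 1.2 patients.
- Brock-only missed cancers: 0.026 × 100 = 2.6, to 0.026 × 300 = 7.8 patients.
- Net planned difference: 0.022 × 100 = 2.2, to 0.022 × 300 = 6.6 patients.
- One patient moves the percentage by 1/100 = 1.0 point, to 1/300 = 0.33 point.

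This shows that the cells are small, so one or two diagnoses changed or left unverified could matter. It does not estimate how many would be. The 0.4% and 2.6% also come from a previous study's LCP and Brock discharge thresholds, not from the 1–10 score the team is shown.

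**The case against.** The strongest reply is that the reference standard is largely objective. Definite malignant is histopathology, definite benign is histopathology or a fixed volume rule over 12 months, and the score is in no category definition. A cancer proven by histopathology stays a cancer whatever the score. The one category resting on clinical judgement is already analysed in and out. Modified management is logged. This stands, and it limits bias in interpretation. It does not address selection: which patients reach histopathology or 12-month imaging is decided after disclosure, and the log captures a changed plan but not a changed reading.

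A second reply is that assessor blinding is detail a condensed article may leave to the full protocol. That stands in part; masking may be specified there. But the release of the score to the clinical team, with an option to act on it, before the diagnosis exists, is a design step this article fixes. It is not inferred from silence, and an analysis plan cannot undo it.

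Two stronger readings are tempting and not supported:

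- *The final diagnosis is made knowing the score.* No sentence says so. Disclosure is at the nodule MDT or a research meeting, while the probable-malignant definition cites a lung cancer MDT. Overlap is plausible but not stated.
- *Follow-up scans sent to VNC mean a follow-up score informs the diagnosis.* VNC is described as software for tracking and assessing nodules generally. The score is obtained by a specific step described for the baseline scan, and no such step is described for follow-up scans.

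**Conclusion.** The concern holds in a limited form. The design exposes the clinical team to the baseline LCP score before the reference standard is established, lets it modify management, and states no blind between the score and work-up, research volumetry or category assignment. The reference standard may therefore depend on the test.

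The documents do not allow the size to be derived, and the existing safeguards make it a modest risk. Its leverage on the cancer outcome, a net planned difference of about 2.2 to 6.6 patients, rests on an assumed 100 to 300 cancers and on threshold-based cells from a previous study. The Clinical pathway section, which anticipates no change to care, and the Data collection section, which allows modification, are in tension and must be reconciled.

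**What to change.** 1. Have research volumetry and assignment of the ground-truth categories done by existing staff who have no access to that patient's LCP score. Keep any LCP output on follow-up series hidden from them until the diagnosis is locked.
2. Add an eCRF field for each probable-malignant diagnosis recording whether LCP was cited.
3. Add a sensitivity analysis of both primary outcomes that excludes those diagnoses and the patients whose management was recorded as modified after disclosure. Because this excludes on an event that follows disclosure, it should support the main analysis, not replace it.
4. Reconcile the Clinical pathway and Data collection sections on whether care may change after disclosure.

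The cost is access rights, one eCRF field, one further analysis and some reallocation of who measures at each site; no additional reader is needed. Whether VNC can hide follow-up output is not stated and needs checking. The treating team's own exposure through the MDT remains, so the verification route is made visible by step 3 but not closed.
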